### Setting

The trial is a multicenter trial, including one academic hospital and four general hospitals in the northern part of the Netherlands. In each center, all vascular surgeons perform surgeries for this study (Table 2). Participating hospitals are outlined on www.pierotrial.nl. In participating centers, each surgeon or interventionalist performing the procedure must have had the experience of 20 Prostar™procedures or 10 Proglide™ procedures prior to including patients in the PiERO trial, to prevent a performance bias. The Proglide™ procedure is a procedure easier to master. A minimum experience of 20 surgical cut downs to the common femoral artery (CFA) is also required. All punctures of the CFA should be performed with ultrasound guidance.

**Table 2 Tab2:** Participating centers, local judging committees and number of surgeons

Participating center	Local medical ethical committee	Number of surgeons
Isala Hospital	METC Isala	four vascular surgeons
	[name]	
	Zwolle	
Medical Centre of Leeuwarden	MCL Academie	three vascular surgeons
	[name]	
	Commissie onderzoeksverklaring	
	Leeuwarden	
Scheper Hospital Emmen	METc Scheper Hospital	two vascular surgeons
	[name]	
	Emmen	
University Medical Center of Groningen	METc UMCG	five vascular surgeons
Wilhelmina Hospital Assen	Board of Governance	two vascular surgeons
	[name]	
	Assen	

### Primary endpoints

The primary endpoints include the number of SSI’s in the groin within 30 days postoperatively and at final evaluation 1 year after the operation. Wounds will be evaluated by means of the Southampton Wound Assessment score [14]. This score lowers the variability in wound assessment by various researchers. When an SSI is diagnosed, both clinically and through the SWA score (Grade III or more), a wound culture should confirm the diagnosis, as described in the CDC definition (Centers for Disease Control and Prevention) [15].

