## Methods/Design

### Study design

In the current study, percutaneous femoral access is compared to open femoral access. Bilateral femoral access is required in each patient treated with a bifurcated EVAR. Therefore, each patient can serve as his/her own control. Randomization is performed for the caliber of the endovascular device (main device versus contralateral extension) that is introduced within the aorta.

The PiERO trial is designed as a randomized, controlled, nonblinded, multicenter superiority trial with two parallel groups and a primary endpoint of wound infection during the 30 days after surgery. Simple randomization will be performed concerning the diameter of the device component introduced in the artery, with a 1:1 allocation.

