#### Follow-up

Wound control is performed at 1 day, 2 weeks and 6 weeks after operation. Final evaluation will take place at 1 year after the procedure. This evaluation will be carried out for infection of the endoprosthesis, according to the definition [15]. The wound evaluation is carried out using the Southampton Wound Assessment score. Wound complications emerging in between measuring points (1 day, 2 weeks and 6 weeks) will also be recorded.

Three VAS scores (Visual Analog Scale) will be obtained before the operation, 1 day after the operation, and 2 weeks after the operation.

Scores are registered in the CRF (case report form) and collected by the objective database manager (Table 3).

**Table 3 Tab3:** Timeline for participants

	Before operation	1 day after surgery	2 weeks after surgery	6 weeks after surgery	1 year after surgery
VAS score	X	X	X		
Wound assessment		X	X	X	X

VAS, visual analog scale

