### Statistical analyses

#### Primary study parameter(s)

The occurrence of SSIs in both groups will be compared with a McNemar’s test and proportional hazards regression. Only two measuring points will be defined, but wound complications are expected to emerge also between these measuring points. A Kaplan Meier curve may be used to log incidences according to time. Both groups will be compared using the log rank test.

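### The primary endpoint has two unreconciled definitions (30 days alone, or 30 days and 1 year), and the 1-year evaluation is directed at the endoprosthesis with no rule for placing its infection on the open or percutaneous side

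*Protocol article*

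**What the plan says.** All references are to the protocol article.

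- **Study design** describes a superiority trial with "a primary endpoint of wound infection during the 30 days after surgery". This is one endpoint with one window.
- **Primary endpoints** uses the plural and counts SSIs "in the groin within 30 days postoperatively and at final evaluation 1 year after the operation". It gives no order and no rule for combining the two times.
- **Follow-up** sets the early visits: "Wound control is performed at 1 day, 2 weeks and 6 weeks after operation". It adds: "Wound complications emerging in between measuring points (1 day, 2 weeks and 6 weeks) will also be recorded". Of the 1-year visit it says: "This evaluation will be carried out for infection of the endoprosthesis, according to the definition". Table 3 in the same section marks a wound assessment at all four postoperative times, including 1 year.
- **Primary study parameter(s)** plans McNemar's test and proportional hazards regression, with Kaplan-Meier and log-rank methods. It states "Only two measuring points will be defined" and does not name the two points.
- **Blinding** says that staff who evaluate the wounds do not know which side took the main device, and concedes that the percutaneous scar is smaller.

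**The concern.** A confirmatory trial needs one endpoint, or a stated rule for several, that decides success. Here one section supports the 30-day result as decisive, and another supports the 30-day result, the 1-year result or both. If the two differ, the choice can be made after the data are seen.

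The 1-year part raises a second problem. The trial compares two groins in the same patient. A groin infection has a side. An infection of the endoprosthesis concerns one implant whose components came through both groins, one open and one percutaneous. Such an infection belongs to neither cell of the paired table unless a rule puts it there.

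The third problem is dating. The 30-day window closes between two visits. For an SSI first seen at week 6, someone must decide afterwards whether it began by day 30, and that person can see from the scar which technique was used.

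**Working it through.** **1. The definitions side by side**

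| Section | Outcome | Time |
|---|---|---|
| Study design | Wound infection | 30 days |
| Primary endpoints | Groin SSI | 30 days and 1 year |
| Follow-up, text | Infection of the endoprosthesis | 1 year |
| Follow-up, Table 3 | Wound assessment | 1 day, 2 weeks, 6 weeks, 1 year |
| Primary study parameter(s) | SSI | Two measuring points, not named |

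Rows 1 and 2 differ on the number of primary times. Rows 2 and 3 differ on what is looked for at 1 year. Row 4 agrees with row 2 that the groin is examined at 1 year, so text and table need reconciling. Row 5 may simply mean 30 days and 1 year. It is unclear, but not shown to contradict Table 3.

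**2. Does the sample size settle the matter?** The inputs, from Sample size calculation, are p1 = 0.068, p2 = 0.001, multiplier 8 and 5 % fall-out.

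- n = 8 × (0.068 × 0.932 + 0.001 × 0.999) / 0.067² = 8 × 0.064375 / 0.004489 = 114.7
- 114.7 / 0.95 = 120.8, against the stated 120.

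The figure reproduces to within one patient. The two rates carry no time window, so the calculation does not show which definition was meant.

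**3. Timing.** The visits fall on days 1, 14 and 42.

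- From the last visit inside the window to its end: 30 − 14 = 16 days, or 16/30 = 53 % of the window.
- From the end of the window to the next visit: 42 − 30 = 12 days.

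These are shares of calendar time. The article gives no distribution of onset times, so they do not measure how many infections would be misdated.

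**4. How much slack is there?** At the planning rates, 120 × 0.068 = 8.2 open-side and 120 × 0.001 = 0.1 percutaneous SSIs are expected. With the two groins taken as independent, the power of the exact two-sided McNemar test at 5 % was obtained by enumeration. The article does not specify the exact version. The shares in the last two rows are assumptions, because the article gives none.

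| Scenario | Power, 120 complete pairs |
|---|---|
| Planning rates | 80.2 % |
| 10 %, 20 %, 30 % of SSIs missed or dated outside the window | 71.9 %, 61.3 %, 48.6 % |
| Endoprosthesis infection in 0.5 %, 1 %, 2 % of patients, assigned to a side at random | 75.4 %, 71.1 %, 63.6 % |

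After the planned fall-out, 120 × 0.95 = 114 pairs remain, and power at the planning rates is 76.4 %.

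**5. Sensitivity of a single result.** For n discordant pairs all on one side, p = 2 × 0.5ⁿ.

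- 8:0 gives 0.0078
- 7:0 gives 0.0156
- 6:0 gives 0.031
- 5:0 gives 0.0625

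**The case against.** The strongest reply is that the follow-up can support both times. Complications between the early visits are recorded, and time-to-event methods are planned, so SSIs can be counted to day 30 by onset date without a day-30 visit. Table 3 schedules a wound assessment at 1 year, and the Primary endpoints section restricts the 1-year count to the groin, so those infections can be assigned to a side. This stands. It rules out saying that neither definition fits the follow-up, or that the 1-year endpoint gives no contrast between techniques. It does not say which definition is primary, or how an endoprosthesis infection is handled.

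Three stronger readings are tempting and are not supported.

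- **A family-wise error of 9.75 %** (1 − 0.95²). This needs independent tests. If the 1-year count includes the 30-day infections, the tests are strongly correlated. Enumerating the exact test at both times under the null, with 114 pairs, 6.9 % or 13 % of pairs discordant by day 30, and 10 to 100 % as many late discordant pairs (all assumed), gives a chance of 2.4 to 4.9 % that either rejects.
- **43 % of late infections misclassified** (12 of the 28 days between visits). This counts days, not infections.
- **One or two events moved across day 30 decide the trial.** From the expected 8:0, losing one or two leaves 7:0 or 6:0, both still below 0.05. Three must move.

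It is also only an inference that an endoprosthesis infection can never be attributed to a groin. The article supports no more than that it gives no attribution rule.

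Finally, moving the primary window to the 6-week visit would avoid back-dating. But no section uses six weeks as an endpoint, and Table 4 shows 55 patients already included in a trial whose operating teams are unblinded.

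**Conclusion.** The concern holds in this form. The Study design and Primary endpoints sections disagree on the primary endpoint, and nothing in the article ranks or combines the two times. The Primary endpoints section and the Follow-up text disagree on what is assessed at 1 year, and no rule covers an implant shared by both groins. The 30-day count is feasible, but it depends on onset dates that come from between-visit recording or are set at week 6 by staff who can see the scar.

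The main consequence is that the primary result is left open to choice, which needs no numerical assumption. The effect on power cannot be fixed from the article. The range in the working rests on the planning rates, independent groins, an exact McNemar test and assumed shares of affected events. It shows only that a design with about 8 expected events tolerates little loss. The sample size itself reproduces and is not in dispute.

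**What to change.** - Name one primary endpoint: SSI per groin (yes/no) with onset by day 30.
- Record the onset date on the case report form for every SSI, including those first seen at week 6.
- Make groin SSI up to 1 year a secondary endpoint, and SSI through the 6-week visit a sensitivity analysis that needs no back-dating.
- Report endoprosthesis infection as a count of patients, outside the McNemar table.
- Bring Study design, Primary endpoints, Follow-up (text and Table 3) and Primary study parameter(s) into line, and name the two measuring points.

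This keeps the stated 30-day window and adds no visit. It costs amendment wording, one date on the case report form, and the primary status of the 1-year result. With 55 patients already included, it should be done before any comparison of outcomes by technique.

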### Secondary endpoints

Wound complications in both groups are assessed during the first 30 days postoperatively. Close attention will be paid to hematoma, femoral neuropathy, dehiscence, fluid discharge, stenotic/occlusive complications in the CFA and signs of infection.

When a *Staphylococcus aureus* SSI occurs (as the major contributor to all in the groin), preoperative isolates will be compared to postoperative SSI involved strains.

All patients will score their wound comfort or pain in a validated VAS score 1 day, and 2 weeks after surgery. Outcomes for open femoral versus percutaneous access will be compared.

Percutaneous access of the CFA is expected to inflict less surgical site infections in the groin compared to open surgical cutdown of the CFA. A lower incidence of infections and localized postoperative problems is expected to offset the additional costs of the percutaneous device. Still, the reduction in complaints needs to be quantified.

Follow-up will be performed until 1 year after the operation, according to the definition of a surgical site infection: “if implant (the endoprosthesis) is in place and the infection appears to be related to the operation” [15].

Recent studies suggest that certain patients may be colonized by multiple different *S. aureus* clones [16]. Also, these bacteria may hide intracellularly [17]. In case of a SSI, we hope to identify the initial localization of the causative microorganism. Therefore, preoperative cultures and punch biopsies will be used, respectively, to study the clonality of isolates by genotyping and to identify intracellular bacteria by fluorescence *in situ* hybridization (FISH) and fluorescence microscopy [18].

### Ethical considerations

Patients who meet the entry criteria will be fully informed about the trial and provided with a patient information and consent form. Patients willing to participate in the study will be included after signing the informed consent form. This study is being conducted in accordance with the principles of the Declaration of Helsinki and Good Clinical Practice guidelines. The protocol, site-specific informed consent forms, participant education and recruitment materials, and other requested documents were reviewed and approved by the Medical Ethics committee of Groningen (CMO 2013-365) and the local institutional board of each participating center (Table 2).

### Safety and quality control

Adverse events (AE) are defined as any undesirable experience occurring to a participant during the study, whether or not considered related to the investigational device. This definition includes events occurring during the hospital stay and up to 30 days of follow-up. Underlying disease that was present at the time of enrollment is not reported as an AE, but any increase in the severity of the underlying disease will be reported as an AE. All AEs will be monitored from the time of enrollment through the 30-day follow-up. AE’s will be recorded on the case record forms (CRFs). A description of the event, including the start date, end date, action taken and the outcome will be reported.

A severe adverse event (SAE) is any event leading to death, major amputation, prolonged hospitalization or renewed hospitalization due to complications and will be communicated to the Medical Ethical committee through “Toetsingonline.”

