#### Concomitant care

In case of an SSI, the wound must be opened, cultured and rinsed with clean water, as considered appropriate according to the treating physician. When infection persists or escalates, oral or intravenous antibiotics are administered. If a second operation is necessary to restrain an infection, this will be registered as an AE.

This trial has no prohibited concomitant medication.

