#### Secondary study parameter(s)

The number of wound complications in both groups will be compared as mentioned previously.

Patient characteristics will be controlled by multivariate analysis with respect to the duration of operation, left/right differences, preoperative bacterial colonization of the nose and the perineum, diabetes mellitus, body mass index, medication, smoking habits and device failure. Although identical groups are examined, we will be able to identify outliers.

Correlations between factors will be estimated using the Pearson correlation coefficient. Proportions of categorical variables are compared using Chi square and Fisher Exact tests, and means of continuous variables are compared using t tests.

The analysis of the primary endpoint (surgical site infection) will be based on an intention-to-treat principle by proportional hazards regression (visualized by Kaplan-Meier survival curves). Intention-to-treat implies that open access because of failed percutaneous access is not excluded from analysis but remains in the percutaneous group. Reasons why percutaneous access may not be successful are inability to obtain access to the arterial lumen with a needle, rupture of the threads of the Prostar XL™ device/2 Proglide™ devices, necessitating open repair and persistent bleeding despite successful use of the Prostar XL™ device/2 Proglide™ devices. The survival analysis is not affected by patient withdrawals (as they will be censored) provided that dropping out is unrelated to prognosis (Table 4). Other outcomes, such as VAS scores 2 weeks post-randomization, may be missing for patients who withdraw from the trial. We will actively seek out reasons for withdrawal and compare the reasons qualitatively.

**Table 4 Tab4:** Number of included patients in the participating centers

Participating center	Number of included patients
- University Medical Center Groningen	13 patients included
- Isala Hospital Zwolle	19 patients included
- Medical Center Leeuwarden	14 patients included
- Wilhelmina Hospital Assen	8 patients included
- Scheper Hospital Emmen	1 patient included
Total:	55 patients included

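### The SAE definition leaves out life-threatening events and lasting disability, so such harm at the access site can remain on the CRF with no stated route to the ethics committee

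*Protocol article*

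**What the plan says.** All references are to the Protocol article.

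- **Definition (Safety and quality control).** An adverse event is any undesirable experience of a participant, whether or not it is related to the device. The subset that counts as an SAE is fixed by outcome: "A severe adverse event (SAE) is any event leading to death, major amputation, prolonged hospitalization or renewed hospitalization due to complications".
- **Reporting route (same section).** The SAE sentence continues "and will be communicated to the Medical Ethical committee through" a named system. Adverse events in general "will be recorded on the case record forms (CRFs"), with a description, start and end dates, action taken and outcome. No onward report is stated for them.
- **Re-operation for infection (Concomitant care).** "If a second operation is necessary to restrain an infection, this will be registered as an AE". This sentence does not mention the SAE definition.
- **Foreseen access-site harm.** Statistical analyses, Secondary study parameter(s), lists ways in which percutaneous access may fail, among them ruptured threads "necessitating open repair and persistent bleeding despite successful use of the Prostar XL™ device/2 Proglide™ devices". Secondary endpoints names femoral neuropathy among the wound complications to be watched for. The Background reports that further interventions were needed more often after percutaneous access than after cutdown.
- **Terminology.** Safety and quality control expands SAE with the word 'severe'; the Abbreviations list uses 'serious'.

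**The concern.** In a closed list, whatever is not named is excluded. Three of the four criteria on this one (death, prolonged stay, readmission) are general, and the fourth (major amputation) is a limb outcome. None asks whether the patient's life was in danger at the time, or whether the patient was left with lasting impairment. An event can be grave in either sense and still resolve within the planned stay.

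The omission touches harms that the article itself expects from access to the femoral artery: bleeding despite deployment of the closure device, and nerve injury in the groin. The ethics committee is the only body outside the trial team that the article names as receiving safety events. If a grave access-site event does not qualify as an SAE, the article gives no way for that committee to learn of it while the trial is running.

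The article sets out this definition in full, so the point concerns a stated rule and not a detail left to the full protocol.

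**Working it through.** No arithmetic applies; the plan gives no figure on this point. The check is to take events that the article foresees and apply the definition and the reporting rule to each.

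| Event | SAE criterion met | Recorded | Stated route to committee |
|---|---|---|---|
| Life-threatening access-site bleeding, controlled during the index operation, discharge as planned | none | CRF | none |
| The same bleeding with a longer stay | prolonged hospitalization | CRF | yes |
| Femoral neuropathy leaving lasting disability, no longer stay, no readmission | none | CRF, and as a secondary endpoint | none |
| Second operation for infection, with readmission or a longer stay | renewed or prolonged hospitalization | CRF | yes |
| Second operation for infection, without either | none | CRF | none |

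**Rows 1 and 3** are the gap. The event is grave by its nature, yet nothing on the list captures it. No other section adds a criterion or a second reporting route.

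**Rows 2 and 4** show how far the present list reaches. Any event that extends the stay or brings the patient back into hospital is already covered.

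**Rows 4 and 5** test Concomitant care against Safety and quality control. An SAE is an event with certain outcomes, and every such event also meets the broad AE definition, so SAEs are a subset of AEs. Registering a re-operation as an AE is therefore compatible with also reporting it as an SAE when a criterion is met. The two sections can both be followed. What is missing is a sentence saying that the second step still applies.

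**Time window.** "All AEs will be monitored from the time of enrollment through the 30-day follow-up", whereas infection is a primary endpoint "within 30 days postoperatively and at final evaluation 1 year after the operation". Concomitant care sets no time limit on the re-operations that it registers. This is a neighbouring question and the conclusion does not rest on it, but a cross-reference should be worded with it in view.

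**The case against.** The best defence is that little escapes in practice. A return to theatre after discharge will normally mean readmission, and a major bleed will often lengthen the stay; both are then SAEs. What remains is still documented on the CRF with action and outcome, and hematoma, neuropathy and stenotic or occlusive complications are collected as secondary endpoints. No planned efficacy analysis uses the SAE definition. All of this stands and limits the weight of the point. It does not close the gap, because recording an event for later analysis is not the same as reporting it to the body that oversees participants' safety.

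Four stronger readings are tempting, and the documents do not support them.

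- A reader might infer that Concomitant care exempts re-operation for infection from SAE reporting. It says such an operation is an AE; it does not say that it is not an SAE. It also concerns infection only and has no bearing on bleeding.
- A reader might want every emergency conversion to open access counted as serious. The Discussion treats open access as the foreseen fallback, and it is also the comparator technique that each patient receives in the other groin. No section makes conversion serious in itself.
- A reader might try to size the gap from an assumed conversion rate. That would count conversions, not events that are life-threatening or disabling and also leave the stay unchanged.
- A reader might fear that SAE counts would not be comparable across the five centres. No pooled or between-centre comparison of SAEs is described.

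Nor does the point rest on a breach of an outside standard. Ethical considerations says "This study is being conducted in accordance with the principles of the Declaration of Helsinki and Good Clinical Practice guidelines", but the article does not reproduce the definition used in those guidelines.

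**Conclusion.** The point holds in a limited form. As written, the SAE definition excludes a life-threatening event or lasting disability that leads to neither death, major amputation, a longer stay nor readmission, and such an event has no stated route to the ethics committee. This follows from the text alone and needs no assumed rate.

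The number of affected events cannot be derived from the documents and is probably small, since many grave events will meet a hospitalization criterion. The consequence is for safety oversight. The primary endpoint, the sample size and the planned analyses are untouched.

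The relation between Concomitant care and the SAE definition calls for clarification and is not a contradiction. The use of 'severe' is a wording slip, but it sits in the very sentence that decides what is reported, and it blurs intensity with consequence. The amendment is worth making; it is not critical to the validity of the trial.

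**What to change.** 1. **Safety and quality control.** Add two criteria to the SAE definition: events that are life-threatening, and events that result in lasting or significant disability. Keep the existing criteria.
2. **Same section.** Replace 'severe' with 'serious', to match the Abbreviations list.
3. **Concomitant care.** Add a cross-reference: a second operation for infection is registered as an AE and is also reported as an SAE whenever it meets the definition. State whether this applies to re-operations after the 30-day AE window.

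The cost is a few sentences of amendment, a notice to the five centres, and a small number of extra reports through the system already in use. Table 4 shows 55 patients included of the 120 planned, so 120 − 55 = 65 were still to come when the article was written. For those already treated, the CRF entries on description, action and outcome should allow any event that meets the added criteria to be identified.
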